#### Quantitative Component

For the quantitative component, we anticipate enrolling between 200 and 350 clients. Client recruitment will follow the same procedures as those outlined in the previous subsection. This number was not the result of a detailed power calculation; rather, it was determined and constrained by the total client population from which we can recruit. Specifically, based on our discussion with the administrators of the NCD study clinic at Semuto Health Center IV, the clinic currently serves approximately 380 clients who meet the aforementioned inclusion criteria. Thus, we realistically expect to enroll 200 to 350 clients based on exact attendance during the study period and refusal rates.

#### Sample Size Estimation

On the basis of the range of recruited participants, we estimate the following minimal detectable effects (Table 5). For these calculations, our primary outcome is the number of clinic visits for medication pickups. On the basis of the 6-month study duration, this can range from 0 to 5 visits (individuals are asked to come once a month), which we will analyze as a count variable using Poisson regression. We additionally set an α of 5% and a power of 80%, with a 2-tailed *t* test for all estimates, and show the minimal detectable effects across a range of possible control counts (the number of visits for pickups among the voluntary contribution group in a range from 1 to 5) and sample sizes (ranging between 200 and 350). The minimum detectable effect is expressed as a rate ratio and measures the percentage increase in mean visits for the subscription contribution (intervention 1) compared with those for the voluntary contribution (intervention 2) over the 6-month study period.

**Table 5 table5:** Minimum detectable effect size across sample sizes and base rates.

Mean number of visits in the voluntary contribution (intervention 2) group	Minimum detectable effect size			
	200^a^	250^a^	300^a^	350^a^
1	1.44	1.39	1.35	1.32
2	1.30	1.27	1.24	1.22
3	1.24	1.22	1.20	1.18
4	1.21	1.19	1.17	1.16
5	1.19	1.16	1.15	1.14

^a^Total sample size (50% intervention 1 and 50% intervention 2).

#### Randomization

Participants will be randomized to be offered either the subscription model or the top-up contribution payment model and assigned to the different models by study team members after the initial recruitment at the facility and upon providing informed consent. The allocation sequence for the random assignment of the intervention was developed by an independent statistician. Individuals are randomly assigned in a 1:1 ratio. We use stratified randomization by sex and day of recruitment, with participants randomized in blocks of 4 to maximize balance between treatment and control. The allocation is concealed because assignment is based on a random draw from a box such that an individual’s assignment is only revealed after they physically draw a slip.

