#### Randomization Implementation

The quantitative research team developed the allocation sequence, and the research assistants enroll participants into the study. After enrollment into the study, each participant will be assigned to a particular arm by drawing concealed slips labeled either direct payment or savings from a box on the day of their recruitment into the study.

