#### Blinding

The allocation sequence of assigning the intervention will be concealed from the research team until the moment of assignment. This will prevent selection bias when assigning participants to study arms. However, because of the nature of this intervention, blinding of neither the research team nor the participants will be possible once the program has started.

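### Drawing a slip from a box hides only the current assignment: if fixed blocks of 4 are enforced, up to a third can be foreseen, and the article names two different makers of the sequence

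*Protocol article*

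**What the plan says.** Three adjoining sections of the protocol article describe the allocation.

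- **Randomization.** The ratio is 1:1, and the strata are formed by sex and recruitment day. A single block size is given: "participants randomized in blocks of 4 to maximize balance between treatment and control". The sequence "was developed by an independent statistician". The claim of concealment rests on the draw: "The allocation is concealed because assignment is based on a random draw from a box". Assignment follows recruitment and consent.
- **Randomization Implementation.** "The quantitative research team developed the allocation sequence, and the research assistants enroll participants into the study". After enrolment, each participant draws a slip that carries the name of an arm.
- **Blinding.** "The allocation sequence of assigning the intervention will be concealed from the research team until the moment of assignment". The section concludes that this prevents selection bias. It adds that neither the team nor the participants can be blinded once the program has started.

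The article mentions no varying block sizes. It does not say that recruiters are kept unaware of the block size, and it does not explain how a draw from a box delivers a prepared sequence in blocks of 4.

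**The concern.** Concealment requires that the person deciding whom to approach next cannot foresee the next arm. A physical draw protects only the slip in hand. With a single published block size and arms that are open after each draw, earlier slips in the same sex-by-day stratum can reveal the later ones.

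What is at stake is the comparability of the arms. The Quantitative Component section adopts the client recruitment procedures of the preceding subsection. Those are convenience sampling in the clinic waiting area and guidance from local providers, so whom to approach, and when, is discretionary. The primary outcome is clinic visits and medication pickups, and the Main Hypothesis section states a direction in favour of subscription.

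Separately, the two accounts of who made the sequence cannot both stand as written. The second also sits badly with concealment from the research team.

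**Working it through.** The plan gives no predictability figure, so there is none to reproduce.

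**Inputs.** Ratio 1:1, block size 4, strata of sex by recruitment day (Randomization); total of 200 to 350 (Quantitative Component); open arms after assignment (Blinding). The number recruited per sex and day is not given.

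**Step 1: a complete block of 4.** The six equally likely orderings are AABB, ABAB, ABBA, BAAB, BABA and BBAA. An assignment is certain once one arm is used up.

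| Position | Chance that the arm is certain | Chance that the best guess is right |
|---|---|---|
| 1 | 0 | 1/2 |
| 2 | 0 | 2/3 |
| 3 | 2/6 = 1/3 (first two match) | 1/3 × 1 + 2/3 × 1/2 = 2/3 |
| 4 | 1 | 1 |

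- Certain share: (0 + 0 + 1/3 + 1)/4 = 1/3.
- Best guess: (1/2 + 2/3 + 2/3 + 1)/4 = 2.833/4 = 70.8%, against 50% by chance.
- Ceiling in participants: 200/3 ≈ 67; 350/3 ≈ 117.

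**Step 2: incomplete last blocks.** With m clients in a sex-by-day stratum, add the position probabilities up to m and divide by m. The certain share is 0 for m = 1 or 2, (1/3)/3 = 11% for m = 3, 33% for m = 4, (4/3)/5 = 27% for m = 5, (4/3)/6 = 22% for m = 6, (5/3)/7 = 24% for m = 7, and 33% for m = 8.

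**Step 3: range over the unknown stratum size.** Assume a Poisson number of clients per stratum.

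| Assumed mean per sex and day | Certain share | Of 200 | Of 350 |
|---|---|---|---|
| 4 | 23% | 46 | 80 |
| 6 | 26% | 53 | 92 |
| 10 | 29% | 58 | 102 |
| 20 | 31% | 63 | 109 |

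At a mean of 2 the share drops to 13%. For scale, the mean is N/(2 × recruitment days). With N = 200, a mean of 4 corresponds to 200/(2 × 4) = 25 days and a mean of 20 to 200/(2 × 20) = 5 days.

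**Step 4: if the box does not enforce blocks.** Step 1 then does not apply, but neither does the stated blocking or the balance it is meant to give.

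**Step 5: alternatives.** For a known fixed block of size 2n the certain share is 1/(n + 1), so a block of 6 gives 1/4 = 25%. Randomly mixed blocks were simulated (12 clients per stratum, 10,000 runs, recruiter aware of the possible sizes but not of the size in use).

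| Blocks | Certain | Best guess right |
|---|---|---|
| Fixed 4 | 33% | 71% |
| Mixed 4 and 6 | 6% | 68% |
| Mixed 4, 6 and 8 | 2% | 67% |

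**Step 6: who made the sequence.** Randomization says that it "was developed by an independent statistician"; Randomization Implementation says "The quantitative research team developed the allocation sequence, and the research assistants enroll participants into the study". Under the second account, part of the research team made the sequence that Blinding says is hidden from the research team.

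**The case against.** The best defence is that one third is conditional. It needs blocks that are enforced and complete, draws made one at a time, and sight of earlier slips before the next client is approached. The article states none of these. If several clients enrol before any of them draws, knowing the last slip cannot affect who enters. This stands, and it makes one third a ceiling.

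Consent and enrolment also come before the draw. That limits the risk but does not remove it, because steering can act earlier, on who is approached and in what order.

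Recruitment may approach a census of the roughly 380 eligible clients. At 350 that is 92% (350/380), but at 200 it is 53% (200/380). Even in a census, the order of same-sex clients within a day decides who receives which arm.

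The conflict over the sequence may be loose wording: a statistician independent of the field staff could belong to the quantitative team, and the research team in Blinding could mean the field staff. That is possible, but the text does not say so.

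A reader might infer more than the article supports:

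- *That the same assistants recruit, take consent and run the draw.* Research assistants enrol, the research team obtains consent and study team members assign; the article does not say that these are the same people.
- *That staff know each client's attendance habits.* This is not stated. The community health workers who assist with qualitative data collection are described as working outside the study setting, although local providers may guide recruitment.
- *That drawing slips rules out a prepared sequence.* A box can be stocked from a blocked list.
- *That no audit trail exists.* The article is silent on logging of slips, which a full protocol may cover, and it describes a REDCap database with an audit trail.

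**Conclusion.** The point holds in a limited form. The box draw does not by itself establish concealment, and the statement that selection bias is prevented goes further than the described procedure allows. Under enforced blocks, sequential draws and visible earlier slips, up to one third of assignments are certain in advance; 23–31% is the working range for assumed means of 4 to 20 clients per sex and day, and the share is smaller in smaller strata. If the blocks are not enforced, the description of the blocking is wrong. In either case the text needs correction.

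The conflict over who made the sequence is literal and depends on no assumption.

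Nothing here shows that bias has occurred, and no size can be put on its effect on visits or pickups. Sample size, alpha and power are unaffected. This is a change that should be made, not a reason to doubt the trial as a whole.

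**What to change.** 1. For all remaining enrolments, the independent statistician generates and alone holds a new list, with randomly varying block sizes (for example 4 and 6) within the existing sex-by-day strata. The sizes are not disclosed while enrolment is open.
2. Each assignment is released singly, after consent is logged, through the REDCap database already in use or in sequentially numbered, opaque, sealed envelopes. If the visible draw matters for trust, the client opens the next numbered envelope.
3. Reconcile Randomization, Randomization Implementation and Blinding: who made the sequence, who had access to it, and how the draw has implemented blocks of 4 so far.
4. For participants already enrolled, replace the claim that selection bias is prevented with a statement of what the procedure protected against and what it did not. Record the date of the switch.

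The cost is a short amendment and a new list or set of envelopes. Daily balance becomes slightly less exact, and the procedure changes during recruitment. The gain is mainly the removal of certainty; guessing improves little. The article reports recruitment as ongoing from August 2023 but not how many clients remain. If few or none do, items 3 and 4 are still needed.

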#### Randomization Implementation

The quantitative research team developed the allocation sequence, and the research assistants enroll participants into the study. After enrollment into the study, each participant will be assigned to a particular arm by drawing concealed slips labeled either direct payment or savings from a box on the day of their recruitment into the study.

#### Blinding

The allocation sequence of assigning the intervention will be concealed from the research team until the moment of assignment. This will prevent selection bias when assigning participants to study arms. However, because of the nature of this intervention, blinding of neither the research team nor the participants will be possible once the program has started.

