#### Data Management

The research study data manager will guide the data management responsibilities for this study. This study’s quantitative data will be collected using both paper and electronic case report forms, whereas qualitative data will be collected using audio recorders. Transcripts and field notes from the qualitative work as well as the paper case report forms will be kept under lock and key and will be overseen by the principal investigators. The transfer of participant-related data, if any, will be carried out in pseudonymized form; third parties will not have access to original data. REDCap (Research Electronic Data Capture; Vanderbilt University) will be used to enter, store, and manage quantitative data. To ensure that quality data are collected, the REDCap platform will provide an interface for data entry (an audit trail to track all changes within the database). In addition, automated validation checks will be embedded within the study database. The study data manager will share data queries generated from the accruing data with the research team on a biweekly basis.

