### Data Analysis

#### Qualitative Data Analysis

Data generated from the qualitative interviews will be transcribed verbatim and analyzed using NVivo software version 14 (Lumivero) following a five-step framework approach: (1) *familiarization with the data*, (2) *identifying a thematic framework*, (3) *indexing*, (4) *charting*, and (5) *mapping and interpretation* [54]. This will help us generate an understanding of stakeholders’ experiences with the prototype. After the completion of the intervention prototype, a detailed analysis plan for this study will be developed. To adapt and inform our design and implementation processes, we will conduct systematic debriefings after each day of qualitative data collection. In weekly team meetings, we will share the first findings from these debriefings with all team members to adjust platform features to end users’ needs and facilitate implementation steps within the community.

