#### Statistical Analysis

The baseline characteristics of participants will be compared between the 2 arms using medians and IQRs for continuous variables and proportions for categorical variables. Outcomes will be analyzed by both the intention-to-treat and per-protocol analysis methods using mixed effects Poisson regression methods for the primary outcomes. We will adjust for baseline imbalances for both the primary and secondary analyses, and both unadjusted and adjusted analyses will be presented. All our regression models will additionally control for baseline patient characteristics such as age, sex, and income to increase the precision of the treatment effects. We will not only conduct a complete case analysis but also present the results using multiple imputation as sensitivity analyses. Missing data on outcomes and key covariates will be assessed before analyses. Where applicable (missingness >10%), we will implement multiple imputation methods appropriate for random effects models. Two-tailed *P* values of ≤.05 will be considered to indicate statistical significance. Analysis will be performed with Stata software (version 17; StataCorp LLC). We will not conduct any interim analysis for this study.

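### The blinding statement is too broad: the nature of the intervention does not prevent masking the analyst of the primary visit and pickup counts

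*Protocol article*

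**What the plan says.** - **Blinding.** Allocation is concealed until assignment. After that, "blinding of neither the research team nor the participants will be possible once the program has started". The reason given is "because of the nature of this intervention". No exception is made for the analyst.
- **Table 4.** The primary outcome is the number of clinic visits and also the number of medication pickups, both taken from health facility records. Take-up and contributions come from the MoPuleesa platform.
- **Sample Size Estimation; Quantitative Data Analysis.** Here the main outcome is a single count: visits with a medication pickup. The second of these sections compares clients by the model they were offered, calls this the intention-to-treat effect, and uses Poisson regression.
- **Statistical Analysis.** "Outcomes will be analyzed by both the intention-to-treat and per-protocol analysis methods", with mixed effects Poisson models for the primary outcomes. Baseline imbalances are adjusted for, age, sex and income are named as examples of covariates, and adjusted and unadjusted results are both shown. Multiple imputation is a sensitivity analysis with a 10% missingness trigger. There is no interim analysis.
- **Data Management.** Quantitative data are held in REDCap, overseen by a data manager. On transfers: "The transfer of participant-related data, if any, will be carried out in pseudonymized form". On access during the trial: "The study data manager will share data queries generated from the accruing data with the research team on a biweekly basis".
- **Main Hypothesis.** The team expects the subscription model to do better.

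**The concern.** The reason given does not reach as far as the rule. Knowing whether one saves by automatic debit or by one's own transfers is unavoidable for the client and for those who run the scheme. It is avoidable for someone who receives a file of counts with a two-letter arm code.

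The sentence is a positive statement that blinding is impossible, so it is not a detail left to an analysis plan that is not shown. Taken at face value, it gives up a protection that costs almost nothing.

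The protection has some value here. The team built the platform and holds a directional hypothesis, and the article leaves or creates room for choice on the primary count, the model and the covariates. If such choices were made by someone who knows the arms and has seen the results, the nominal 5% error rate would no longer be assured.

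**Working it through.** **1. Does the stated reason cover the analyst?** The primary comparison needs a count per client, the arm and baseline covariates. The counts come from facility records (Table 4), the data sit in REDCap under a data manager (Data Management), and the comparison is by arm offered (Quantitative Data Analysis). No payment data are needed, so an A/B code is enough. The reason therefore does not cover this person.

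**2. Where does masking stop being possible?** Take-up, contributions and the instrumental-variable analysis use platform data. Month-end automatic debits against client-timed transfers may reveal the arm. Masking is realistic for the primary counts, and less so for these analyses.

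**3. Which choices are open?**

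| Item | Status in the article |
|---|---|
| Primary count | Two counts in Table 4; one in Sample Size Estimation and Quantitative Data Analysis |
| Model | Poisson in Quantitative Data Analysis; mixed effects Poisson in Statistical Analysis |
| Covariates | Examples only, plus observed imbalances |
| Intention-to-treat or per-protocol | Intention-to-treat is the main effect; both are reported |
| Adjusted or unadjusted | Both are reported; neither is named as primary |
| Imputation | Sensitivity analysis with a stated trigger |

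The first three can depend on the data or need reconciling. The last three are largely committed to joint reporting or already ranked.

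**4. The plan's own figures.** Table 5 follows from log RR = (1.960 + 0.842) × √[(1/m + 1/(m·RR))/n], with n = N/2 per arm and m the mean number of visits in the top-up (voluntary contribution) arm. For m = 1 and N = 200: 2.802 × √[(1 + 1/1.44)/100] = 0.365, so RR = 1.44, as printed. All 20 cells agree within 0.01. Masking changes none of them.

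**5. Size under fully selective choice.** Two simulations with no arm effect, each at N = 300, count a trial as positive if any variant reaches P ≤ .05.

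*Simulation A* (4000 trials; counts bounded 0–5, 9% missing covariate, about 70% take-up unrelated to arm, robust-SE Poisson). Four analysis sets × three covariate sets = 12 variants.
- Each variant alone: 4.5% to 5.2%
- Any of the 6 full or complete-case intention-to-treat variants: 9.4%
- Any of the 12: 14.3%

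*Simulation B* (1500 trials; mean 3 visits, unbounded counts, 80% of visits with a pickup, 70% random take-up, robust-SE Poisson).
- One fixed analysis: 4.7%
- Choice of 2 outcomes: 6.7%
- 2 outcomes × adjusted or unadjusted (4 variants): 10.1%
- The same × intention-to-treat or per-protocol (8 variants): 15.1%

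Monte Carlo error is small: √(0.143 × 0.857/4000) = 0.6 points for A and √(0.151 × 0.849/1500) = 0.9 points for B. Eight independent tests would give 1 − 0.95⁸ = 34%, so the variants are strongly correlated. Neither simulation covers multiple imputation or Poisson against mixed effects Poisson.

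With intention-to-treat held fixed, as the article says for the main effect, the relevant figures are 9.4% and 10.1%. The 14% to 15% figures also require a per-protocol result to be put forward as the main one.

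**The case against.** **Most of the alternatives will be reported together.** This stands. Intention-to-treat is the main effect, adjusted and unadjusted results are both promised, and imputation is ranked as a sensitivity analysis. The simulated rates require unfavourable variants to be suppressed. They describe multiplicity under selective reporting, and naming one primary analysis addresses that more directly than masking does. Masking is an added safeguard, which is why the fix pairs the two.

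**A reader might infer that analysis choices are made by people looking at results by arm.** The article does not say so. It plans no interim analysis, the biweekly items are data queries and not arm-level results, and an analysis plan not shown here may settle the choices before lock.

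**A reader might take "After the completion of the intervention prototype, a detailed analysis plan for this study will be developed" as showing that the trial analysis is still open.** The sentence stands under Qualitative Data Analysis and may not concern the trial. If it does, the trial tests the finished prototype, so its timing is compatible with a plan written before outcome data exist.

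**A reader might infer that record extractors can be masked too, or that extraction will favour one arm.** Neither is supported. No separate extractor role is described, and nothing says whether facility records show the payment route. Under the earlier paper scheme, clinic staff tried to track who had paid, so such information may sit beside pickup entries. A masked extractor might also need extra staff.

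**Pseudonymised transfer and the independent statistician do not prove that a masked analyst is already available.** This stands. Pseudonyms hide identity, not arm. The statistician is named for the sequence only ("The allocation sequence for the random assignment of the intervention was developed by an independent statistician"), and the next section attributes the sequence to others: "The quantitative research team developed the allocation sequence, and the research assistants enroll participants into the study". It is unclear whether the analyst belongs to the research team that the blinding sentence covers.

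**Conclusion.** The point holds in a limited form. The Blinding statement is wider than its reason: it is justified for participants, clinic staff and field staff, but not for the analyst of the primary counts. No planned figure is wrong, and the article gives no evidence that choices will follow a look at results by arm.

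The exposure is a false positive rate of at most about 9% to 10% with intention-to-treat held fixed, or 14% to 15% if per-protocol results could also be selected, against a nominal 5%. These are upper bounds for the variants simulated. They rest on fully selective choice and on assumed values for missingness, take-up, pickup rate and, in simulation B, mean visits. They show why masking helps, not that bias will occur. This is a cheap improvement to a stated rule.

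**What to change.** 1. Limit the Blinding statement to participants and those who deliver the program (clinic and field staff).
2. Have the data manager export a primary-outcome file with study ID, counts, baseline covariates and arm coded A/B. Any take-up flag needed for the per-protocol set is defined in advance and derived by the data manager.
3. Release the code only after the primary count, model, covariates, per-protocol definition and missing-data rules are signed and the counts are locked. Before that, settle one count against two and Poisson against mixed effects Poisson.
4. State that the analyst has no access to the allocation log, and reconcile the two accounts of who produced the sequence.
5. State whether those who extract facility records know the arm. A separate masked extractor is not required.

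**Cost.** One revised paragraph and a masked REDCap export, with no change to sample size, alpha or power. Recruitment was ongoing when the article was written, so this could still be adopted before lock. The downside is that MoPuleesa payment data can be merged only after the code is released. The contribution, uptake and instrumental-variable analyses therefore come later and are not masked.
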